### Data collections

Data collected are the patient’s age (month and year of birth), pathology, clinical and molecular characteristics of the tumour on biopsy and surgical specimen, the size of the target lesion during clinical examination, at mammography and ultrasound, and responses to questionnaires. Data collected will be pseudonymized. Thus, study data will not contain any names or other personal identifiers such as addresses. Patients included in the trial will be identified by a code specific to this trial. Investigators will have access to the correspondence table between the patient’s last name, first name, date of birth and the code assigned in the trial.

### Statistical analysis

#### Primary analysis

The main analysis consists of comparing the patient satisfaction scores between the two groups, RFID vs. gold standard, and, if the difference in mean scores is clinically significant (difference of about 20%), to test whether it is statistically significant using Student’s t-test or a non-parametric test depending on the nature of the data. A propensity score matching will be performed beforehand to compensate for the non-randomized design of the study. We will include in the calculation of the propensity score the anxiety measured by the HAD scale at inclusion, the only measurable confounding factor we estimate being related to the primary outcome.

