### Sample size calculation

The satisfaction score is a continuous score taking values between 0 and 10 points. To be able to show a minimum effect size of ¾, corresponding to a difference of about 23% of the overall score, for an estimated standard deviation of about 1.5 points, with a power of 80%, and considering a type I error rate of 5%, a number of 30 patients per group would be necessary. To take into account a rate of non-matchable patients of about 20%, as well as a rate of non-evaluable patients of about 10%, 40 patients will be included in each group, for a total of 80. Given the lack of preliminary data, and the uncertainty around the assumptions used for sample size calculation, an interim analysis will be performed after approximately half of the initially planned number of subjects has been included. The purpose of the interim analysis is to re-estimate the number of subjects needed based on the distribution of scores, in order to ensure sufficient statistical power of the study. Since no early ending is planned after the interim analysis, the alpha risk will not be adjusted, and the formal comparison between the two groups by hypothesis testing will be done only at the final analysis.

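### The primary test is run only if the observed difference reaches an undefined 20% or so, but the 80% power belongs to a test without that condition; on a common base the power is about 63–65%

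*Protocol article*

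**What the plan says.** The Primary analysis section of the protocol article describes a two-stage rule. After propensity score matching, mean satisfaction is compared between groups and then, "if the difference in mean scores is clinically significant (difference of about 20%), to test whether it is statistically significant", by a t-test or a non-parametric test. The hypothesis test is therefore reached only if the observed difference is large enough.

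The Sample size calculation section describes a one-stage rule. Its inputs are:
- Scale: "The satisfaction score is a continuous score taking values between 0 and 10 points".
- Target: a standardised effect of ¾, described there as "corresponding to a difference of about 23% of the overall score"; the SD is taken to be 1.5.
- Result: "with a power of 80%, and considering a type I error rate of 5%, a number of 30 patients per group would be necessary".

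That section contains no condition on the observed difference. It adds an interim re-estimation of the number of subjects from the distribution of scores, and it places the formal group comparison at the final analysis, again without a condition. Neither section defines the base of its percentage.

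**The concern.** A power statement is valid only for the decision rule it was computed for. Here the trial is sized for one rule (test at 5%) and analysed by another (first pass a threshold on the point estimate, then test at 5%). If the threshold is stricter than the significance boundary, the threshold decides the outcome, and the chance of a positive result under the planned effect is lower than the article states.

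The threshold of about 20% lies just below the planning difference of about 23%. A real effect of the planned size would then miss the threshold quite often through sampling error alone and would not be tested. Differences that do reach testing are selected to be large. Because the base of the percentages is not given, the size of the loss cannot be fixed from the article alone.

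**Working it through.** **Inputs** (Sample size calculation section unless noted): score 0 to 10; effect size 0.75; SD 1.5; power 80%; type I error 5% (sidedness not stated); 30 evaluable per group; 23% for the planning difference; 20% for the condition (Primary analysis section).

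**1. Reproduce the stated sample size without the condition.**
- Planning difference = 0.75 × 1.5 = 1.125 points.
- Two-sided 5%, 80% power: 28 per group by the normal formula, 28.9 (so 29) by the exact t-test, and 28.9 / 0.955 = 30.3 with the usual allowance for a rank test. A one-sided test gives 22, which does not match.
- Power of the two-sided t-test at 30 per group is 81.5%.

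So the stated 30 is that of an ordinary two-sided test that is always run.

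**2. Significance boundary at 30 per group.**
- SE = 1.5 × √(2/30) = 0.387.
- Critical difference = t(0.975; 58 df) × SE = 2.002 × 0.387 = 0.775 point.

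**3. The condition in points, same base for both percentages.**
- 1.125 points is called about 23%, so the base is 1.125 / 0.23 = 4.89, and 20% of it is 0.978 point (equivalently 1.125 × 20/23).
- With a rounded base of 5, 1.125 points is 22.5% and the condition is 1.0 point.

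Both exceed 0.775, so a trial that meets the condition is almost always significant as well. The condition is the binding criterion.

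**4. Power of the two-condition rule**, approximately Φ((true difference − threshold) / SE):
- Threshold 0.978: Φ(0.147 / 0.387) = Φ(0.38) = 64.8%.
- Threshold 1.0: Φ(0.125 / 0.387) = Φ(0.32) = 62.7%.

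Simulation with the SD estimated (400,000 replicates) gives 64.8% and 62.6%, against 81.5% without the condition. The planned miss rate of about 20% becomes 35–37%.

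**5. Other readings of the undefined base** (assumptions):

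| Reading | True difference | SD | Threshold | Power | Conflict with the article |
|---|---|---|---|---|---|
| Both percentages on the 10-point scale, SD rescaled to keep effect size 0.75 | 2.3 | 3.07 | 2.0 | 65% | stated SD 1.5 |
| Both percentages on the 10-point scale, SD kept | 2.3 | 1.5 | 2.0 | 78% | effect size becomes 2.3/1.5 = 1.53, which needs about 8 per group |
| Threshold on the 10-point scale, effect as stated in SD units | 1.125 | 1.5 | 2.0 | 1.2% | 1.125 is 11.25% of the scale, not 23% |
| Threshold as 20% of an assumed control mean of 6, 7 or 8 | 1.125 | 1.5 | 1.2, 1.4, 1.6 | 42%, 24%, 11% | 1.125 is then 19%, 16% or 14% |

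**6. Selection of large differences.** Given that the threshold is passed, the expected observed difference is 1.125 + SE × φ(a)/Φ(a), with a from step 4.
- Threshold 0.978: 1.125 + 0.387 × 0.371/0.648 = 1.35 points.
- Threshold 1.0: 1.125 + 0.387 × 0.379/0.627 = 1.36 points.
- Selection by significance alone (0.775 point): a = 0.350/0.387 = 0.90, giving 1.125 + 0.387 × 0.265/0.817 = 1.25 points.

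**7. Type I error.** With no true difference, the two-sided rejection rate falls from 5% to about 1% (threshold 0.98 to 1.0) or essentially 0% (threshold 2.0).

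**8. Can more patients make up for it?** For 80% power, n = 2 × (1.5 × 0.842 / (1.125 − threshold))², which is about 148 per group at 0.978 and about 204 at 1.0. Analysing all 40 enrolled per group gives only 67.0% and 64.5%.

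**The case against.** **Requiring both a relevant and a significant difference is a recognised, conservative success rule.** This stands. The rule cannot produce extra false positives, and step 7 confirms that. The fault is that the power is not stated for the rule and the threshold is not given in points.

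**The wording may be loose, and the test may be run in any case.** Possibly, but the sentence is explicitly conditional and it defines the main analysis. If unconditional testing is intended, saying so settles the matter.

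**A reader might infer that the condition means 2 points and that power is therefore about 1%.** The article does not support this. It gives no base for the 20%, and the 1% arises only by measuring the threshold on the 10-point scale while keeping an effect of 1.125 points that the article itself calls about 23%. That mixes two bases. The unclear conversion from effect size to percent is a separate fault of the Sample size calculation section.

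**One reading nearly delivers 80%.** With a true difference of 2.3 points, SD 1.5 and a 2-point threshold, power is 78%. This deserves to be shown, but it abandons the stated effect size of ¾ and would not lead to 30 per group. The 65% reading with SD 3.07 likewise departs from a stated input. That is why the main estimate keeps both effect size ¾ and SD 1.5.

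**A reader might infer that a difference below the threshold would go unreported.** The article does not say this. The main analysis is the comparison of scores, and only the test is conditional. The selection in step 6 concerns the differences that reach testing.

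**The interim re-estimation protects the power.** It works from the distribution of scores and does not mention the condition. If the true difference lies at or below the threshold, no number of patients takes the power above 50%.

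**Conclusion.** The point holds: the 80% power is that of an unconditional two-sided test, while the stated primary analysis tests only after a threshold on the observed difference. Power for the rule as written is about 63–65% rather than about 81%. This assumes one common base for the 20% and the 23%, effect size ¾, SD 1.5, 30 evaluable per group and approximately normal means.

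The result is not sensitive to the evaluable number: the stated losses leave 40 × 0.8 × 0.9 = 28.8 per group if they multiply, or 40 × 0.7 = 28 if they add, and at 28 the figures are 62–64%. It is very sensitive to the base, with a range of about 1% to about 78% over the other readings, each of which conflicts with at least one stated input. The consequence is lost power and upward selection of tested differences, not false-positive risk.

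**What to change.** By a dated and justified amendment before the final analysis:

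1. State that the primary test is always performed on the matched groups, and that the mean difference is always reported with its two-sided 95% CI.
2. Judge clinical relevance as a separate statement, by setting the estimate and its interval against a threshold that the sponsor defines in points of the 0–10 score.
3. State the base of the 23%, or replace it by the difference in points, so that effect size, SD and percentage agree.

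If the sponsor prefers to keep the two-condition rule, define the threshold in points and restate the power for the joint criterion: about 63–65% on the common-base reading, or about 148 to 204 evaluable per group if 80% is wanted.

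The recommended change costs a short amendment and no patients; the existing 30 per group then gives about 81% power. The date and the reasons matter: the Trial status section reports 64 patients already recruited, patients know their device, and an interim look at the scores is planned at about half enrolment. The amendment should therefore record what had been seen when the rule was changed.

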#### Secondary analysis

The secondary analysis consists of the analysis of the global score values, and the comparison between the two study groups, of the patient questionnaires (with matching or adjustment for baseline anxiety values), the surgeons and the radiologists, using the Student’s t-test (/ non-parametric test) or the chi-square test (/ Fisher’s exact test), depending on the nature of the data. If a statistically significant difference between groups is found, a post-hoc analysis will follow on the questionnaire items, with multiple testing corrections.

Data on localization quality will also be analysed and compared between groups using one-tailed tests to ensure that they do not indicate an inferiority of the experimental device.

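### Matching on a propensity score built from HAD anxiety alone gives up about 20% of patients to control a variable that direct adjustment would control with every evaluable patient kept

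*Protocol article*

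**What the plan says.** The trial allocates devices in sequential blocks, not at random. For the primary comparison of satisfaction scores, the protocol article (Primary analysis) says: "A propensity score matching will be performed beforehand to compensate for the non-randomized design of the study". The same section names one variable for the score, HAD anxiety at inclusion, and describes it as the only measurable confounder thought to be related to the outcome. The test that follows is Student's t-test or a non-parametric test. Whether it is paired is not stated.

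The Sample size calculation section asks for 30 patients per group, based on a "minimum effect size of ¾", and enrols 40 per group. The margin is explained by: "To take into account a rate of non-matchable patients of about 20%, as well as a rate of non-evaluable patients of about 10" per cent. It also plans an interim re-estimation of the number of patients.

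For the secondary analysis of the patient questionnaires, the article accepts either route: "with matching or adjustment for baseline anxiety values". Only the primary analysis is confined to matching.

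**The concern.** A propensity score earns its place by reducing many covariates to one number. With a single covariate there is nothing to reduce. A standard logistic score is then a monotone function of HAD anxiety, so matching on the score is matching on HAD.

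The cost is sample size. By the plan's own estimate about one patient in five cannot be matched and drops out of the primary comparison. That comparison then describes the matchable women and not all those enrolled. In a trial of 80 patients this means giving up about 7 evaluable patients per group, although the article already accepts for its secondary patient scores an adjustment that keeps them.

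**Working it through.** **Inputs.** All are from the Sample size calculation section unless marked: effect size 0.75 SD; SD 1.5 points; type I error 5% (sidedness not stated; two-sided assumed, because a one-sided calculation needs only 22 per group); power 80%; 30 per group needed; 40 per group enrolled; about 20% non-matchable; about 10% non-evaluable. *Assumed, not in the document:* the correlation r between HAD anxiety and satisfaction (0, 0.3, 0.5), and the difference in mean HAD between groups (0 or 0.5 SD).

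**Step 1. Reproduce the plan's figure.** The normal approximation for d = 0.75 gives 28 per group. The noncentral t gives 29 per group (80.1% power), and 30 per group gives 81.5%. Dividing 28 by the Wilcoxon efficiency of 0.955 gives 29.3, which rounds up to 30. The stated 30 is therefore reproduced to within two patients. The 40 follows from 30 × 1.2 × 1.1 = 39.6, or from 28 / 0.7 = 40.

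**Step 2. Patients left after each method.**
- Matching, losses compounding: 40 × 0.8 × 0.9 = 28.8 per group.
- Matching, losses adding: 40 × (1 − 0.30) = 28 per group.
- Adjustment, non-evaluable loss only: 40 × 0.9 = 36 per group.
- Difference: 36 − 28.8 = 7.2 to 36 − 28 = 8 patients per group.

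**Step 3. Power at d = 0.75, two-sided 5%, no condition on the observed difference.**
- Matched, unpaired t-test: noncentrality d√(n/2), df = 2n − 2.
- Matched, paired t-test, assuming close matches on HAD so that the within-pair correlation is r²: noncentrality d√n / √(2(1 − r²)), df = n − 1, with 28.8 pairs.
- Adjusted: noncentrality d√(n/(2v)) / √(1 − r²), df = 2n − 3, n = 36, where v = 1 + (HAD imbalance in SD)²/4.

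| Analysis | r = 0 | r = 0.3 | r = 0.5 |
|---|---|---|---|
| Matched, unpaired (28 to 28.8 per group) | 78.7–79.9% | not credited with r | not credited with r |
| Matched, paired (28.8 pairs) | 78% | 82% | 89% |
| Adjusted, HAD imbalance 0.5 SD | 86.1% | 89.1% | 94.0% |
| Adjusted, HAD balanced | 88.0% | 90.8% | 95.2% |

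**Step 4. Standard error from sample size alone (r = 0, against 28.8 per group).** Balanced HAD: √(28.8/36) = 0.894, about 10.6% smaller with adjustment. Imbalance of 0.5 SD: v = 1 + 0.25/4 = 1.0625, and √(0.8 × 1.0625) = 0.922, about 8% smaller.

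**Step 5. Where the gain ends.** With r = 0 and a HAD imbalance of 1 SD, adjusted power falls to 80.1%, level with unpaired matching.

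**Step 6. The other effect size in the same sentence.** The plan describes 0.75 SD as "corresponding to a difference of about 23% of the overall score", "for an estimated standard deviation of about 1.5 points". But 0.75 × 1.5 = 1.125 points, about 11% of a 0–10 scale, while 2.3 / 1.5 = 1.53 SD. At 1.53 SD, power exceeds 99.9% with 28 or with 36 per group.

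**The case against.** Pre-specified matching with its losses budgeted is a legitimate analysis, and several points in its favour stand.

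- **The shortfall is small.** A reader might infer that the study fails its sample size because 28–28.8 is under 30. It does not: the loss rates are approximate, 29 per group gives 80.1%, 28 meets 80% by the normal approximation, and the interim re-estimation may change the number. The point is the avoidable loss, not a failed calculation.
- **Pairing.** A reader might infer that the t-test ignores the matching. The article does not say whether it is paired, and that detail may sit in the full protocol or analysis plan. A paired test recovers part of HAD's prognostic value, so the fair gap is about 7–9 points at r = 0.3 and 5–6 at r = 0.5.
- **No guaranteed gain.** It is tempting to read 88% power, or a 10.6% smaller standard error, as a minimum for adjustment. Both require balanced HAD, and a 20% non-matchable rate may itself reflect imbalance.
- **Model assumptions.** Matching avoids assuming a linear HAD effect, and a rank test suits a bounded 0–10 score. Adjustment is therefore not free on the bias side.
- **Timing.** Recruitment stood at 64 patients, past the planned interim at about half of 80.

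None of this gives matching on one variable any control of confounding that adjustment lacks. The time effect of the sequential blocks is left untouched by both methods.

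**Conclusion.** The concern holds as a point about efficiency and about whom the primary result describes. The plan accepts the loss of about 7–8 evaluable patients per group to control HAD anxiety, and adjustment controls the same variable without that loss. At 0.75 SD the gain is roughly 6–9 percentage points of power if HAD does not predict satisfaction (79–80% against 86–88%). It is smaller against a paired test when HAD is strongly prognostic (89% against 94–95% at r = 0.5).

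These figures rest on the plan's loss rates, a two-sided test, 80 patients enrolled, and assumed values for r and HAD imbalance. They describe the test without the plan's condition that the observed difference first be clinically significant; the plan's own 80% appears to be on the same footing, since the 30 per group is reproduced without that condition. The power gain disappears if the true difference is 2.3 points, although the loss of precision remains. Nothing here shows that the planned analysis is invalid.

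**What to change.** Make the primary analysis a linear model of the satisfaction score on device, adjusted for baseline HAD anxiety, in all evaluable patients, and report the adjusted difference with a robust 95% confidence interval. Keep the matched comparison, or a rank-based one, as a sensitivity analysis. Restate the attrition allowance as about 10%, giving 36 analysed per group from 40 enrolled.

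No further data or recruitment are needed, because HAD is already collected at inclusion. The costs are two. The model assumes a roughly linear HAD effect and adequate overlap in HAD between groups, which the sensitivity analysis would check. And because recruitment has passed the planned interim point, the change needs a documented amendment, made before the final between-group comparison.

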## Background

Breast cancer is the most frequently diagnosed cancer and the leading cause of cancer death in women with 58,500 new cases in France in 2018. Approximately 50% of breast cancers are discovered at an early stage in mainly young patients and for whom conservative surgery is indicated. Intraoperative localization of non-palpable breast lesions is generally accomplished using a hook wire to mark the area of concern under ultrasound or stereotactic localization.

However, this technique has several drawbacks. Indeed, it appears as a relatively painful and anxious procedure for patients. It can also be a source of difficulty for the surgeon, because only the entry point is visible: the orientation and length of the wire are assessed on a control image. Moreover, it leads to a time coordination obligation between radiologists and surgeons since the localization device cannot remain in place for more than 24 h. Finally, because the end of the hook wire comes out at one end of the breast and goes through the skin it can be associated with a risk of infection, breakage, accidental exposure to blood or wire dislodgement.

During the last decades, other localization techniques have been studied as alternatives to hook wire [1]. None of these alternatives has been able to prove its superiority compared to hook wire, which remains the gold-standard. A wire-free breast lesion system using miniature radiofrequency identification (RFID) tags appears as an interesting alternative (LOCalizer™ with CE marking and FDA labelling). It is a radio-opaque tag that emits a radiofrequency signal when excited at a specified wavelength. It is carried by a 12-gauge coaxial needle and can be positioned under ultrasound or stereotactic guidance. A receiver that registers the RFID number is available for radiologists and handheld reader displays the distance to the tag in millimeters (up to 6 cm) for surgeons. This technique aims to improve patient comfort and surgical comfort by increasing localization accuracy. Moreover, radiologists would no longer be dependent on the surgical schedule. The oblong shape of the tag should reduce the risk of accidental exposure to blood, and material breakage. Nevertheless, the cost of this technique remains significantly higher than the hook wire. Acceptance and changes in practices by radiologists and surgeons are necessary.

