**Fig. 1 Fig1:**
[figure not shown]
Design of the RFID study. The participation to the study will be proposed during a senology consultation to any patient requiring preoperative localization. The RFID tag and the hook wire will be respectively placed during the senology consultation and the day before the surgery. In the two groups, patients will fill out a Hospital Anxiety and Depression scale (HAD) questionnaire and then fill out a satisfaction questionnaire during the placement of the device (RFID tag or hook wire) and during the postoperative consultation at 1 month. Radiologists and surgeons will also fill out a questionnaire respectively after the localization and surgery procedures

Any patient requiring preoperative localization will receive a senology consultation and participation in the study could be proposed. A sequential inclusion in time will be performed: 20 inclusions in the gold-standard group, then 20 patients in the RFID group before repeating the inclusion scheme. Eighty patients will be enrolled.

The RFID tag or the hook wire will be respectively placed during the senology consultation and the day before or the day of the surgery. If the hook wire is placed the day before the surgery patients should stay in overnight.

As soon as they are included, patients will fill out a Hospital Anxiety and Depression scale (HAD) questionnaire to determine potential anxiety and depressive disorders.

The included patients will then fill out a satisfaction questionnaire in two steps:during the placement of the device (RFID tag or hook wire),during the postoperative consultation at 1 month

Radiologists and surgeons will fill out a questionnaire dedicated to them, respectively after the localization and surgery procedures.

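### The propensity score uses HAD anxiety alone, although age, biopsy pathology and lesion size are recorded and the single-device blocks leave part of any time trend in the comparison

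*Protocol article*

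**What the plan says.** All references are to the protocol article.

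- **Primary analysis** gives the remedy for the lack of randomisation: "A propensity score matching will be performed beforehand to compensate for the non-randomized design of the study". It then names the content of the score: "We will include in the calculation of the propensity score the anxiety measured by the HAD scale at inclusion". The reason offered is that this is "the only measurable confounding factor we estimate being related to the primary outcome". The Secondary analysis section again names only baseline anxiety for matching or adjusting the patient questionnaires.
- **Data collections** lists more baseline information: "age (month and year of birth), pathology, clinical and molecular characteristics of the tumour on biopsy and surgical specimen", and also "the size of the target lesion during clinical examination, at mammography and ultrasound, and responses to questionnaires".
- **Patient selection** admits histologically proven lesions from fibroadenomas and papillomas to atypical lesions and neoplasia. It also says that patients learn which device they will get when they consent.
- **Study design** fixes allocation by time: "20 inclusions in the gold-standard group, then 20 patients in the RFID group before repeating the inclusion scheme". Patient selection gives 3 months for each of the first two blocks.

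The article mentions no adjustment for age, pathology, lesion size or calendar time.

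**The concern.** A superiority claim on patient satisfaction is to come from an unblinded, non-randomised comparison in which each calendar period contains one device only. Its credibility rests on the adjustment, and the adjustment rests on one score.

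Two sources of bias are left open. First, case mix can differ between blocks. Whether a woman has a fibroadenoma or a cancer, her age and the size of the lesion could each plausibly affect how she rates a breast procedure, and all three are recorded. Second, anything that drifts over the enrolment period and affects both devices, such as staffing or waiting times, falls unequally on the two groups. Matching on anxiety at inclusion removes either bias only as far as anxiety happens to carry it. What remains goes directly into the primary difference.

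**Working it through.** **Plan's own figure.** Sample size calculation gives an effect of 0.75 SD, SD 1.5 points, 80% power and 5% type I error (two-sided assumed, since sidedness is not stated). The planned difference is 0.75 × 1.5 = 1.125 points. The normal formula gives 2 × (1.96 + 0.842)² / 0.75² = 27.9, so 28 per group; the t-test gives 29. The stated 30 is reproduced closely enough, so the point does not turn on sample size.

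**Imbalance in time.** Number the patients 1 to 80 in the order wire, RFID, wire, RFID.
- Mean position, wire: (10.5 + 50.5)/2 = 30.5. Mean position, RFID: (30.5 + 70.5)/2 = 50.5. The difference is 20 positions, or 20/80 = one quarter of enrolment.
- With a single switch after 40 patients the difference would be 40 positions, or one half. Alternation therefore halves the bias from a linear drift but does not remove it.
- A linear drift of X points over enrolment biases the difference by X/4, which is the drift over one block of 20.

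| Assumed drift over enrolment (points) | Bias (points) | Share of 1.125 |
|---|---|---|
| 0.5 | 0.125 | 11% |
| 1 | 0.25 | 22% |
| 2 | 0.50 | 44% |

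**Imbalance in case mix.** Bias = imbalance × effect of the factor. With an assumed 20-point difference between groups in the share of cancers and an assumed effect of 0.5 SD on satisfaction, bias = 0.20 × 0.5 = 0.10 SD, which is 0.10/0.75 = 13% of the planned effect.

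**Cost of a time term.** The SD of positions 1 to 80 is √((80² − 1)/12) = 23.09. The correlation of order with device is 20 × 0.5/23.09 = 0.433. Variance inflation is 1/(1 − 0.433²) = 1.23, and √1.23 = 1.11, so standard errors are about 11% wider. At 30 evaluable per group, power falls from about 81% to about 73%.

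**A block-cycle term does not help.** Each cycle (first or second wire-RFID pair) holds 20 wire and 20 RFID patients, so cycle is uncorrelated with device. RFID is still 20 positions later within each cycle, and the linear-drift bias is one block-step with or without the term. With cycle and order together, the within-cycle SD of position is √((40² − 1)/12) = 11.54, the correlation is 10/11.54 = 0.866, and variance inflation is 1/(1 − 0.7505) = 4.01. Standard errors would double.

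**False-positive rate.** In SD units at 30 per group the standard error is √(2/30) = 0.258. Primary analysis tests only if the mean difference reaches about 20%, and that percentage can be read in several ways. Assumed drifts per block are 0.1, 0.2 and 0.3 SD.

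| Reading of the threshold | 0.1 | 0.2 | 0.3 |
|---|---|---|---|
| No threshold | 6.7% | 12.1% | 21.3% |
| 1 point (20% of an assumed mean near 5) | 1.6% | 3.6% | 7.8% |
| 2 points (20% of the 0–10 scale) | under 0.01% | under 0.01% | under 0.01% |

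If 20% is scaled by the Sample size calculation's own equation of 23% with 0.75 SD, the threshold is 0.75 × 20/23 = 0.65 SD. The rate is then about 1% with no drift and about 9% at 0.3 SD per block.

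**The case against.** The strongest reply is that the article makes a judgement of relevance. A reader might infer that it claims nothing else can be measured, or that Primary analysis and Data collections contradict each other. The text does not support either reading: it says anxiety is the only measurable factor thought to be related to satisfaction, which is compatible with recording other variables. That part of the reply stands. What remains is that the judgement is unsupported and hard to square with so wide a case mix.

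Further points that stand:
- A reader might infer that device and calendar time cannot be separated at all. For a smooth trend the confounding is partial, and a linear term can be estimated. Irregular period effects cannot be separated with only two blocks per device.
- A reader might quote false-positive rates of 7%, 12% and 21%. Those assume unconditional testing, and this plan does not test unconditionally. The drifts are also assumed: 0.3 SD per block is 0.9 SD from first to last block, more than the planned effect.
- Guidance mode might be taken as already collected and independent of the device. The Background says only that the tag "can be positioned under ultrasound or stereotactic guidance". Data collections does not list guidance mode, and it may be chosen once the device is known.
- Growing experience with RFID affects one group only and, early on, would tend to work against RFID. It is not a drift shared by both groups.
- Lesions are histologically proven before inclusion, so HAD anxiety may already carry part of the cancer-versus-benign effect.
- Matching 40 per group on more variables could lose more than the 20% allowed for non-matchable patients.

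Sensitivity analyses for time are often left to the analysis plan, which is not shown. That answers an omission, but here the covariate set and the reason for it are fixed in the article.

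**Conclusion.** The concern holds in a limited form. The article fixes HAD anxiety as the sole named covariate to compensate for non-randomised allocation in single-device blocks and gives no support for excluding recorded baseline variables that could plausibly matter. Alternation leaves a quarter of any linear drift in the primary difference.

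The quarter follows from the enrolment order if drift is linear and the 80 patients enter in the stated sequence. The size of any actual drift or case-mix imbalance cannot be known from the document, and every figure for it above is an assumption. No single inflated false-positive rate can be attributed to the plan, because the rate depends on how the 20% threshold is read. The threshold does not reduce bias in the estimate, and a bias in favour of RFID helps the difference to cross it.

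**What to change.** - Pre-specify four baseline covariates for the primary comparison: HAD anxiety, age, pathology from the biopsy (benign or atypical versus cancer) and lesion size on pre-operative imaging. Do not use surgical-specimen findings, which arise after placement of the device.
- Use them in the propensity score or as regression adjustment. Use regression if matching on four variables would exceed the planned 20% non-matchable loss.
- Report one sensitivity analysis with a linear enrolment-order term and no block-cycle term.
- Use guidance mode only as a sensitivity covariate, and only if it is recorded and was determined by the lesion rather than by the device.
- Delete the clause "the only measurable confounding factor we estimate being related to the primary outcome", and give the reason for the covariates chosen.

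The named covariates are already in the database, so no patients or visits are added. The cost is a few degrees of freedom, possibly some additional unmatched patients, and about 11% wider standard errors in the time sensitivity analysis, which is why it should not be the primary model. Trial status reports 64 of 80 patients recruited, so the set should be fixed before the groups are compared.
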